### Data Collection and Access

Participant data will be collected using study forms (MultimediaAppendices 1^4^) and stored on a designated Google Drive, which will be used as the study repository. A copy of all the files will be stored on an external hard drive for backup. The research supervisor will audit completion of the electronic spreadsheet and will be responsible for data safety and accuracy. Incorrect or missing data will be assessed by this researcher, who will not be involved in other tasks in the study, and corrected when necessary. Data from participants who discontinue the study will remain available in Google Drive for the reviewers and will be presented in the results, CONSORT flowchart, and tables. Study data will be stored for at least 5 years after completion of the study.

### Level of Pragmatism

The level of pragmatism is shown in Figure 2 and detailed in Table 2.

**Figure 2. F2:**
[figure not shown]
ePragmatism level wheel. 1: very explanatory; 2: rather explanatory; 3: equally explanatory/pragmatic; 4: rather pragmatic; 5: very pragmatic.

**Table 2. T2:** Domains and score of pragmatism level.^a^

Domains	Score	Rationale
1. Eligibility—Who is selected to participate in the trial?	4	All patients already had an indication for total hip arthroplasty in the outpatient clinic. Exclusions were limited to cases in which the disease could compromise the results because of acetabular outcome (such as severe hip dysplasia) or when there was a known indication for other specific implants (eg, ceramic femoral heads for patients younger than 40 years old).
2. Recruitment—How are participants recruited into the trial?	5	Patients were selected from the public waiting list and referred by the health department and/or spontaneous demand. The study was announced, but the waiting list at the beginning of the study already included the entire projected population.
3. Setting—Where is the trial being done?	3	Despite being a tertiary teaching hospital, currently, this is the most common setting to offer this treatment in the public system (Sistema Único de Saúde) in Brazil
4. Organization—What expertise and resources are needed to deliver the intervention?	3	Because of the study, a dedicated set of instruments was kept in the hospital for consistency, which does not usually occur in the routine care. However, the surgical team, operating rooms, and available equipment are the same as the usual care.
5. Flexibility (delivery)—How should the intervention be delivered?	5	Surgery will be undertaken as planned, in the same manner as the usual technique used at the hospital over the last 10 years
6. Flexibility (adherence)—What measures are in place to make sure participants adhere to the intervention?	—	Surgical intervention (to be left blank)
7. Follow-up—How closely are participants followed up?	4	Patient visits to the clinic will follow the same pattern as the usual care. Because diverse questionnaires need to be applied, each visit is expected to be longer than routine consultations
8. Outcome—How relevant is it to participants?	4	Pain, satisfaction, quality of life, function, and need for revision are highly relevant to patients. However, radiographic parameters will also be measured, which are mostly important only for surgeons
9 Analysis—To what extent are all data included?	5	After surgery, all data will be collected and analyzed. An intention-to-treat approach is planned if necessary

a 1: very explanatory; 2: rather explanatory; 3: equally explanatory / pragmatic; 4: rather pragmatic; 5: very pragmatic.

### Sample Size

The sample size was calculated using the Statulator Sample Size Calculation tool [25]. To disprove the null hypothesis of equality, assuming a pooled SD of 10.5 units for the HHS [6], the study would require a sample size of 60 participants per each group (ie, a total sample size of 120 for equal group sizes) to achieve a power of 80% and a significance level of .05 (2-sided) for detecting a true difference in means of 5.39 units between the test and the reference groups (ie, 56.9 vs 62.3).

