## Introduction

Total hip arthroplasty (THA) is a highly successful procedure for treating hip arthritis, improving patients’ pain, function, and quality of life (QoL) [1,2]. However, THA is still vulnerable to complications such as fractures, loosening, infection, as well as other biological issues [3]. Because patients who undergo THA face the risk of cumbersome and costly revision procedures, the life expectancy and durability of the implant are important issues [3]. Different surgical techniques and implants, such as cemented and uncemented stems, are used to perform THA [4]. However, despite the good results of this procedure, no single surgical technique or type of implant has been proven superior for all patients [4].

To date, considerable controversy persists regarding the best type of surgical implant. While in North America, there is a preference for noncemented implants [4], this is mainly based on the findings of a 17-year follow-up randomized controlled trial (RCT) published by Corten et al [5] in 2011. In other countries, especially in Europe, the preference for cemented femoral implants has been maintained. The latter is supported by at least 6 RCTs that show no differences between these types of implants [4], as well as reports of a greater incidence of surgical complications with uncemented implants, especially in older patients [6].

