## Methods

### Study Design and Setting

This study was written according to the Standard Protocol Items: Recommendations for Interventional Trials (SPIRIT) guidelines (Checklist 1) for protocols of randomized clinical trials. The proposal is a single-center, single-surgeon, single-approach, pragmatic, double-blinded, prospective randomized trial to analyze the differences between uncemented hip replacement and the hybrid (femoral cemented) hip replacement.

Two different types of hip implants will be used for comparison: the Maxima Cemented Vincula Stem (Víncula, Rio Claro, SP, Brazil) and the Taper Uncemented Primary Stem (Víncula, Rio Claro, SP, Brazil). Patients and evaluators will be blinded to group allocation: the hybrid group (HG) and the uncemented group (UG). A total of 120 patients will be enrolled in this study and randomly allocated to each group in a 1:1 ratio.

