### Withdrawal From the Study

Participants who wish to withdraw after the operation, as instructed in the preparticipation recommendations, may continue with usual treatment at the hospital. In the case of withdrawal at any point after surgery, the data will be considered missing, and data imputation techniques will be evaluated. Data from participants who discontinue the study will remain available in the electronic dataset during revision and will be presented in the results. The study will follow the Consolidated Standards of Reporting Trials (CONSORT) flow chart and tables.

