### Primary Outcomes

The primary outcomes of this study will be patient-reported function and complications.

Clinical evaluation will comprise the measurement of hip ROM to assess joint mobility, and the HHS questionnaire will be applied to assess function. Hip ROM will be measured using the goniometer, with the patient lying supine, to determine joint mobility. Hip function will be assessed using the HHS, which is a THA-specific questionnaire composed of patient-reported function and physician-assessed joint ROM, including pain, function, deformity, and mobility assessment [19,20]. The HHS is scored up to 100 points, where each section has a different score, and after applying the questionnaire, all scores are summed up. Scores below 70 are considered low, scores between 70 and 80 are considered fair, scores between 80 and 90 are considered good, and scores between 90 and 100 are considered excellent [19].

The incidence of complications (during and after surgery) will be extracted from an intraoperative questionnaire completed by the surgeon, an immediate postoperative questionnaire reported by the patient, and a special severe adverse effect questionnaire, which will be filled whenever the patient requires readmission or additional surgery.

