### Statistical Analysis

Results will be presented descriptively, with continuous data expressed as means (SD) and medians, and categorical data will be presented as means or percentages. For inferential analysis, the normality of the variables will be assessed using the Kolmogorov-Smirnov test. Dichotomous variables will be analyzed using the Fisher exact test and chi-square test, and continuous variables will be analyzed using the *t* test. Demographic data will be analyzed using ANOVA test, and the chi-square test will be used for the categorical data. In cases of non-normal distribution, appropriate nonparametric tests will be used according to the nature of the variable.

Primary outcomes, complications, and reoperations will be analyzed at 48 weeks. Paired and subgroup analyses are foreseen between periods of 3, 6, 24, and 48 weeks for the described outcomes. Results will be reported with 95% CI.

All statistical tests will be 2-sided, with a significance level of *P*=.05. Data will be analyzed using the Online Statistics Calculator, DATAtab/Numiqo (2025) [26]. Data from participants who receive additional treatments (eg, revision surgery for fractures) during study participation will be retained for intention-to-treat analysis.

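### The 80% power holds only with complete 48-week follow-up: 120 is both the number required and the number enrolled, and the planning values are not tied to 48 weeks

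*Protocol article*

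**What the plan says.** All references are to the Protocol article.

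- **Sample Size:** "the study would require a sample size of 60 participants per each group (ie, a total sample size of 120 for equal group sizes"). The target is 80% power with a two-sided 5% test, and the effect sought is a gap of 5.39 HHS units between planning means of 56.9 and 62.3. The pooled SD of 10.5 HHS units is cited to reference 6. The two means carry no citation and no time point. No allowance for loss to follow-up is mentioned.
- **Study Design and Setting:** "A total of 120 patients will be enrolled in this study and randomly allocated to each group in a 1:1 ratio". The Randomization section fixes the same total as 10 blocks of 12.
- **Withdrawal From the Study:** "In the case of withdrawal at any point after surgery, the data will be considered missing". Imputation is only to be evaluated; no method is chosen and no withdrawal rate is given.
- **Statistical Analysis:** "Primary outcomes, complications, and reoperations will be analyzed at 48 weeks". Continuous variables are compared with a t test, or nonparametrically if not normal.
- **Primary Outcomes:** the HHS runs to 100, and "Scores below 70 are considered low".
- **Conclusion (Discussion):** the trial is described as the first adequately powered prospective evaluation of these procedures in Brazil.

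**The concern.** A sample-size formula returns the number of patients who must contribute an outcome to the analysis. Here that number is also the recruitment target, so the stated power assumes that every randomised patient has an HHS at 48 weeks. The article provides for withdrawal but does not carry it into the calculation.

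The planning values raise a second question. Both means are in the low band, while the Introduction calls the operation highly successful and the analysis is almost a year after surgery. With no time point attached, a reader cannot tell whether the 5.39 difference and the SD of 10.5 describe 48-week scores or scores at some other time.

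What is at stake is how the result is read. If the trial finds no difference, readers will weigh that finding against the 80% and the claim of adequate power. Both should describe the number actually analysed and an SD shown to belong to the endpoint.

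**Working it through.** **Inputs.** From Sample Size: difference δ = 5.39, SD σ = 10.5, two-sided α = 0.05, power 80%, 60 per group. From Study Design and Randomization: 120 enrolled, 10 × 12 = 120 randomised, 1:1. Dropout: not given, so 5% to 20% is assumed.

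**1. Reproduce the plan's figure.** Normal formula: n per group = 2(1.960 + 0.842)² × 10.5² / 5.39² = 59.6, rounded up to 60. This matches. Power at 60 per group is 80.3% by the normal formula and 79.6% by the exact (noncentral t) calculation for the planned t test. The exact calculation would ask for 61 per group.

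**2. Margin.** The unrounded requirement is 59.57 per group. Losing one patient leaves 60 and 59, an effective size of 2 × 60 × 59 / 119 = 59.50 per group, already below 59.57. There is no slack by either method.

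**3. Power and detectable difference under assumed loss.** Exact t test, δ = 5.39, σ = 10.5, noncentrality = 5.39 / (10.5 × √(2/n)):

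| Assumed loss | Evaluable per group | Power for 5.39 | Difference detectable at 80% power |
|---|---|---|---|
| 0% | 60 | 79.6% | 5.41 |
| 5% | 57 | 77.5% | 5.56 |
| 10% | 54 | 75.3% | 5.71 |
| 15% | 51 | 72.8% | 5.88 |
| 20% | 48 | 70.2% | 6.07 |

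The normal formula gives 78.2%, 76.0%, 73.6% and 71.0% at 5%, 10%, 15% and 20% loss, so the choice of method does not alter the conclusion.

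**4. Planning means.** 62.3 − 56.9 = 5.4, which agrees with 5.39 after rounding. Both means are below 70. Their level does not enter the formula; only δ and σ do. The low level matters only as a sign that δ and σ may belong to another time point.

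**5. Sensitivity to the SD.** The article gives no 48-week SD, so these values are assumptions. At 60 per group and δ = 5.39, power is about 96% if σ = 8, 68% if σ = 12 and 50% if σ = 15. The stated 80% could be too low or too high.

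**The case against.** The strongest reply is that nothing is miscalculated. The inputs give 60 per group, and 60 per group gives 80%. The shortfall depends on a dropout rate that the article does not state, and it is small at low loss: about 2 points at 5% and 4 at 10%. The withdrawal text is conditional and predicts no rate, imputation is to be considered, patients who have further surgery are kept in the analysis, and results will carry 95% confidence intervals that show the precision achieved.

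Most of this stands, and it limits the point. It does not remove it: imputation does not restore the information in unobserved scores, and the stated power still has no margin.

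Four stronger readings are tempting, and the article does not support them.

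- *That 80% power is simply not delivered.* With complete follow-up it is, to within half a point.
- *That the planning means are impossible at 48 weeks.* No expected 48-week HHS is given. The article supports only that both means are in its low band and undated.
- *That the means come from reference 6 and so describe the wrong population.* That citation is attached to the SD, not the means. The Introduction cites it for "reports of a greater incidence of surgical complications with uncemented implants, especially in older patients [6"], but a study of complications can also report an applicable HHS SD.
- *That adjusting for baseline HHS would recover the loss.* The Statistical Analysis section plans a t test. Under the usual variance factor of 1 − ρ², offsetting 10% loss needs a baseline correlation of √0.10 = 0.32, and 20% loss needs √0.20 = 0.45. The article gives no correlation.

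**Conclusion.** The point holds in a limited form. The sample-size arithmetic is right for 60 evaluable patients per group. Because the required number is also the number enrolled, any missing 48-week HHS takes power below the stated 80%. The size is modest: about 78% to 70% power for assumed losses of 5% to 20%, with the detectable difference rising from 5.41 to at most 6.07. The direction does not depend on the dropout rate; the size does, and that rate is an assumption.

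Separately, the planning means are in the article's low band and have no time point, so it is not shown that 5.39 and 10.5 apply at 48 weeks. That uncertainty could raise or lower power and cannot be resolved from the article. The figures in the loss table assume that both values do apply.

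**What to change.** 1. **Sample Size.** Say that 80% power for 5.39 points requires complete 48-week follow-up. State the expected loss, and give power and detectable difference for the evaluable number. For example, 54 per group gives 75% power for 5.39, or 80% power for 5.7.
2. **Planning values.** Give the source and time point of the means and of the SD.
3. **SD check.** Once 48-week scores are available, have the data curator compute one SD over all patients without using allocation, and report the detectable difference it implies. An SD that ignores group includes the group difference: with the planned values it would be √(10.5² + 5.39²/4) = 10.8 rather than 10.5, a small overstatement to note.
4. **Conclusion.** Qualify the claim of adequate power so that it refers to the evaluable number and the assumed SD.

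More enrolment is not proposed. The loss is modest, and the Results section already reports a first analysis of the complete population in November 2025. Baseline adjustment should be offered as a remedy only if that analysis is added to the plan, and then only to the extent that the baseline correlation supports it.

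The cost is one rewritten paragraph, one blinded calculation and one softened sentence. The stated power becomes slightly less favourable.

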### Statistical Analysis

Results will be presented descriptively, with continuous data expressed as means (SD) and medians, and categorical data will be presented as means or percentages. For inferential analysis, the normality of the variables will be assessed using the Kolmogorov-Smirnov test. Dichotomous variables will be analyzed using the Fisher exact test and chi-square test, and continuous variables will be analyzed using the *t* test. Demographic data will be analyzed using ANOVA test, and the chi-square test will be used for the categorical data. In cases of non-normal distribution, appropriate nonparametric tests will be used according to the nature of the variable.

Primary outcomes, complications, and reoperations will be analyzed at 48 weeks. Paired and subgroup analyses are foreseen between periods of 3, 6, 24, and 48 weeks for the described outcomes. Results will be reported with 95% CI.

All statistical tests will be 2-sided, with a significance level of *P*=.05. Data will be analyzed using the Online Statistics Calculator, DATAtab/Numiqo (2025) [26]. Data from participants who receive additional treatments (eg, revision surgery for fractures) during study participation will be retained for intention-to-treat analysis.

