**Figure 1. F1:**
[figure not shown]
Flowchart of the study protocol. mHHS: modified Harris Hip Score; mo: months; SF-12: 12-Item Short Form Health Survey; wk: weeks; y: years; *: clinical evaluator; **: surgeon; ***: radiographic evaluator; ****: data curator (supervisor).

Standard digital anteroposterior pelvis radiographs with calibration spheres will be obtained. A clinical interview and thorough preoperative evaluation will be undertaken by a medical doctor (orthopedic surgery resident). Functional, pain, and QoL questionnaires will be administered at this point, and surgical appointments will be scheduled (Multimedia Appendix 1).

Patient assignment and preoperative evaluations will be conducted in monthly blocks of 12 patients for practical and logistic purposes. Random allocation of patients to each group, the HG and the UG, will be performed at this time using double blinding.

At this stage, the surgeon will be blinded to group allocation and clinical assessment and will perform surgical planning for both uncemented and hybrid procedures using Peekmed software (Peekmed Inc, Braga, Portugal). Peekmed is a highly sensitive tool currently in use that focuses on digital surgical planning to evaluate the accuracy of corrections and to reproduce patient-specific anatomy. Data from both surgical plans will be extracted by the same surgeon using a specially designed digital form (MultimediaAppendices 2  3). Reports of the surgical plans will be printed and kept until surgery; however, only the correct plan, as decided by the random group allocation, will be provided to the surgeon by the assistant researcher before surgery.

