### Secondary Outcomes

Secondary outcomes will include comparisons of QoL, joint mobility, function, satisfaction, and pain before and after the surgery, as well as radiographic parameters extracted from the immediate postoperative radiograph. The annual frequency of revision surgeries will be recorded.

QoL will be evaluated using 12-Item Short Form Health Survey version 2 questionnaire [21]. QoL is defined as an individual’s perception of their position in life in the context of the culture and value systems in which they live and about their goals, expectations, standards, and concerns [21]. The 12-Item Short Form Health Survey is an instrument for measuring QoL composed of 12 items that assess eight different dimensions of influence on QoL, considering the individual’s perception of aspects of their health in the last 4 weeks [21]. Each dimension’s score is summed up, and the final score can be between 0 and 100; the higher the score, the better the QoL [22].

Participant satisfaction assessment will be measured using a 10-point numerical rating scale ranging from 1 (very dissatisfied) to 10 (completely satisfied) [23].

Other aspects of health, such as pain, will be evaluated through the Visual Analog Scale. The Visual Analog Scale provides a simple and efficient measure of pain intensity and is used when a fast pain index that can be assigned to a numerical value is needed [24].

Radiographic parameters will include the ability to restore anatomical normality parameters on postoperative radiographs according to the surgical plan (namely the limb length discrepancy, the horizontal off-set of the hip, difference between the back of the prosthesis and the tip of the trochanter, inclination of the acetabular component, and the difference between offset obtained to the normal side) all of this using the Peekmed surgical planning software.

The annual frequency of revision surgery will be observed starting from 1 year after surgery and annually until 5 years, and up to 10 years.

All questionnaires will be administered by examiners blinded to the surgical procedure. Questionnaires will be completed using digital devices (computer or tablet).

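### The 48-week Harris Hip Score is analysed by a t test with no baseline covariate, and a normality test may replace it with an unnamed rank-type test: precision is lost and the tested quantity is not fixed

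*Protocol article*

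**What the plan says.** All references are to the protocol article.

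- **Statistical Analysis, choice of test.** "the normality of the variables will be assessed using the Kolmogorov-Smirnov test". For inference, "continuous variables will be analyzed using the *t* test". If a distribution is judged non-normal, nonparametric tests suited to the variable are used instead; none is named. No covariate, regression or mixed model appears. The primary outcomes are analysed at 48 weeks, and 95% CIs are promised.
- **Statistical Analysis, further comparisons.** "Paired and subgroup analyses are foreseen between periods of 3, 6, 24, and 48 weeks for the described outcomes".
- **Primary Outcomes.** Function is a primary outcome, alongside complications. It is measured by the HHS, which has a maximum of 100 points.
- **Recruitment and Preoperative Assessment.** At the visit before surgery, "Functional, pain, and QoL questionnaires will be administered at this point". The instrument is not named there, but the Primary Outcomes section and the abbreviation list of Figure 1 (modified HHS) make the HHS the natural reading.
- **Secondary Outcomes.** "Secondary outcomes will include comparisons of QoL, joint mobility, function, satisfaction, and pain before and after the surgery". A comparison of function before and after surgery needs a preoperative value.
- **Sample Size.** 60 per group, for "detecting a true difference in means of 5.39 units between the test and the reference groups (ie, 56.9 vs 62.3"), with a pooled SD of 10.5, 80% power and two-sided 5% significance.

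**The concern.** Two features of the stated analysis work against the powered comparison.

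1. **Unused baseline.** A two-sample t test takes no covariate. The preoperative score is already collected, and adjusting for it removes the part of the 48-week variance that it explains. The trial is sized at 80% power, so precision that needs no extra patients is worth having.
2. **A test chosen by the data.** The Sample Size section plans for a difference in means, in HHS points. If the normality test leads to a rank comparison, that mean difference is no longer the quantity tested, and the promised 95% CI has no target fixed in advance. Neither the version of the Kolmogorov-Smirnov test nor the replacement test is named.

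A smaller point concerns the paired comparisons between visits. Within-arm change shows that patients improve after arthroplasty; it does not compare hybrid with uncemented stems. The role of these comparisons should be stated.

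**Working it through.** **Inputs from the Sample Size section:** SD 10.5; difference 5.39; n = 60 per arm; two-sided alpha 0.05; power 80%. **Assumed:** the correlation r between baseline and 48-week HHS, which the documents do not give; range 0.1 to 0.7.

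**Step 1: reproduce the plan's figure.** By the normal approximation,

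n per arm = 2 × [(1.960 + 0.842) × 10.5 / 5.39]² = 59.6, rounded up to 60.

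Power at 60 per arm is 80.3% by this approximation. With the t distribution, the noncentrality is 5.39 / (10.5 × √(2/60)) = 5.39 / 1.917 = 2.81, and power is 79.6%. The stated 60 per group is reproduced and is not in dispute.

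**Step 2: power with baseline adjustment.** ANCOVA replaces the SD by the residual SD, 10.5 × √(1 − r²). The effective sample size per arm is 60 / (1 − r²). The approximate 95% CI half-width is 1.96 × residual SD × √(2/60). Power is from the noncentral t distribution.

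| Assumed r | Residual SD | Power | Effective n per arm | CI half-width (points) |
|---|---|---|---|---|
| no adjustment | 10.50 | 79.6% | 60 | 3.76 |
| 0.1 | 10.45 | 80.0% | 60.6 | 3.74 |
| 0.2 | 10.29 | 81.2% | 62.5 | 3.68 |
| 0.3 | 10.02 | 83.2% | 65.9 | 3.58 |
| 0.4 | 9.62 | 86.0% | 71.4 | 3.44 |
| 0.5 | 9.09 | 89.6% | 80.0 | 3.25 |
| 0.7 | 7.50 | 97.4% | 117.6 | 2.68 |

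The gain is 0.4 to 1.6 percentage points at r = 0.1 to 0.2, and 6 points or more from r = 0.4.

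**Step 3: the normality switch.** The two-stage rule was simulated with no true difference, 60 per arm and 3,000 runs: a normality test in each arm, then a Mann-Whitney test if either arm failed, otherwise a t test. The Mann-Whitney test is an assumption, because the plan names no replacement. The skewed scenario (an assumed gamma-type tail below a ceiling of 100) is illustrative.

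| Data | Switch rate, plain Kolmogorov-Smirnov | Switch rate, Lilliefors version | Type I error of the two-stage rule |
|---|---|---|---|
| Normal | 0% | 7% | 4.9–5.0% |
| Ceiling-skewed | 23% | 94% | 5.3–5.8% |

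Type I error stays close to 5%. How often the tested quantity changes depends heavily on the shape of the data and on the unstated version of the test.

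**The case against.** The strongest reply is that nothing here is invalid. Under randomisation the unadjusted t test is unbiased, and its standard error already allows for chance baseline imbalance. It also matches the sample size calculation. That stands: adjustment improves precision and does not repair a bias.

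It is also true that the size of the gain rests on a correlation that the documents do not supply, and that at 0.1 to 0.2 there is almost nothing to gain. That stands too, which is why the full range is shown.

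Three stronger readings might be inferred and are not supported:

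- **That the 100-point cap makes a switch likely.** On the protocol's planning figures, the higher mean lies (100 − 62.3) / 10.5 = 3.6 SD below the cap, so those figures do not predict a ceiling. If 48-week scores did pile up near 100, that would tend to weaken the correlation with baseline, and with it the gain from adjustment.
- **That the switch inflates the false-positive rate materially.** The simulated rates do not show this. What remains is that the tested quantity is not fixed in advance; reporting means and medians in any case softens this only in part.
- **That within-arm tests replace comparisons of the arms.** The paired analyses are foreseen alongside the t test, the stated objective is hybrid versus uncemented, and the before-and-after wording could equally mean change from baseline compared between arms. The text is unclear on this point, not wrong.

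One could add that an article leaves model details to an analysis plan. That covers optional extras. It does not cover a test and a switching rule that the article itself states.

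**Conclusion.** The point holds as one of efficiency and of a fixed target. The plan names a covariate-free t test for 48-week HHS and lets a normality test replace it, while a preoperative function score is available.

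On the protocol's own inputs, the unadjusted analysis has 79.6% power; adjustment gives between 80.0% (r = 0.1) and 97.4% (r = 0.7). The benefit is negligible up to about 0.2 and material from about 0.4. This rests on the planning SD and difference, on the assumed correlations, and on reading the preoperative functional questionnaire as the HHS. That the t test is unadjusted is inferred from the absence of any named covariate.

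Separately, and whatever the correlation, the switch means that the mean difference used for sizing is not guaranteed to be what is tested. The change should be made, but the trial is not unsound without it.

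**What to change.** - State the primary HHS analysis as an ANCOVA of 48-week HHS on arm and baseline HHS, reporting the adjusted mean difference with its 95% CI.
- Remove the normality test as a gate. Name one sensitivity analysis in advance, either a rank test or a bootstrap CI.
- Apply the same baseline adjustment to the SF-12, pain and range of motion.
- Label the paired comparisons between visits as descriptive.
- Adjustment for age and a repeated-measures model over the 3, 6, 24 and 48-week visits are optional.

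The cost is wording, provided the chosen software can fit the model. No new data are needed. The Results section describes the November 2025 analysis as covering population characteristics, radiographic and intraoperative findings and early complications, not 48-week HHS. The change should be dated and documented before the arms are compared on that outcome.
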